## Abstract

**Background:**

Percutaneous catheter ablation (CA) to achieve pulmonary vein isolation is an effective treatment for drug‐refractory paroxysmal and persistent atrial fibrillation (AF). However, recurrence rates after a single AF ablation procedure remain elevated. Conventional management after CA ablation has mostly been based on clinical AF recurrence. However, continuous recordings with insertable cardiac monitors (ICMs) and patient‐triggered mobile app transmissions post‐CA can now be used to detect early recurrences of subclinical AF (SCAF). We hypothesize that early intervention following CA based on personalized ICM data can prevent the substrate progression that promotes the onset and maintenance of atrial arrhythmias.

**Methods:**

This is a randomized, double‐blind (to SCAF data), single‐tertiary center clinical trial in which 120 patients with drug‐refractory paroxysmal or persistent AF are planned to undergo CA with an ICM. Randomization will be to *an intervention arm* (*n* = 60) consisting of ICM‐guided early intervention based on SCAF and patient‐triggered mobile app transmissions versus *a control arm* (*n* = 60) consisting of a standard intervention protocol based on clinical AF recurrence validated by the ICM. Primary endpoint is AF burden, which will be assessed from ICMs at 15 months post‐AF ablation. Secondary endpoints include healthcare utilization, functional capacity, and quality of life.

**Conclusion:**

We believe that ICM‐guided early intervention will provide a novel, personalized approach to post‐AF ablation management that will result in a significant reduction in AF burden, healthcare utilization, and improvements in functional capacity and quality of life.

## INTRODUCTION

1

Atrial fibrillation (AF) is a major public health concern in the United States and is associated with significant morbidity, mortality, and healthcare costs. Catheter ablation (CA), mostly in the form of pulmonary vein isolation (PVI), has been shown to be effective in restoring and maintaining sinus rhythm (January et al., 2014, 2019; Kim et al., 2011; Kirchhof et al., 2016).

Recurrence rates of AF after a single CA procedure continue to be a concern, and many patients require more than one procedure to achieve symptom control (Calkins et al., 2009). While recurrences of AF after CA are common during the first 3 months (“blanking period”), they are associated with an increased risk of procedural failure (Liang et al., 2016). The most common reason for AF recurrence after CA is a reconnection of electrically active pulmonary veins. This results in continued AF‐induced atrial remodeling that facilitates further progression of AF after the ablation procedure (Atul et al., 2005; Callans et al., 2004; Gerstenfeld et al., 2003; Nanthakumar et al., 2004). In the CABANA study (Effect of Catheter Ablation vs. Antiarrhythmic Drug therapy on mortality, stroke, bleeding, and cardiac arrest among AF patients), detection of clinical recurrence of paroxysmal or persistent AF using the study's electrocardiogram event recorder approached 40% at 1‐year (Packer et al., 2019). There are now increasing data suggesting that early intervention for AF recurrence may improve long‐term outcomes and reduce AF burden following CA.

The clinical significance of subclinical atrial fibrillation (SCAF) detected by insertable cardiac monitors (ICM), and the effectiveness of early intervention following ablation remains controversial. To date, studies have relied on conventional symptom reporting and discontinuous monitoring to detect recurrent AF after CA. However, recent data suggest that symptoms may be an underestimate of postablation AF burden, and nearly 40% of patients experiencing recurrence after AF ablation remain asymptomatic (Pedrote et al., 2013; Tondo et al., 2014; Verma et al., 2013; Wechselberger et al., 2018). In the DISCERN AF study (Discerning the incidence of symptomatic and asymptomatic episodes of AF before and after CA), the proportion of AF episodes that were asymptomatic (SCAF), increased from 52% before to 79% after ablation (*p* = .002) and the postablation state was shown to be the strongest predictor of SCAF (Verma et al., 2013). Therefore, early intervention following the detection of SCAF by an ICM may be important to prevent substrate progression. The ICM‐REDUCE‐AF study is designed to test the hypothesis that an ICM‐guided early intervention strategy following CA will lead to a greater reduction in AF burden, healthcare utilization, and improvement in functional capacity.

## METHODS

2

### Objectives

2.1

The primary objective of the ICM‐REDUCE‐AF study is to determine whether an ICM‐guided early intervention strategy following CA of drug‐refractory paroxysmal or persistent AF will lead to a greater reduction in AF burden.

The secondary objectives of this trial, in a prioritized order are as follows:
Evaluate whether an ICM‐guided early intervention strategy following CA of drug‐refractory paroxysmal or persistent AF is associated with a significant reduction in healthcare utilization; defined as unplanned hospitalizations, emergency department (ED) visits, office visits, or cardioversions.Determine whether an ICM‐guided early intervention strategy following CA of drug‐refractory paroxysmal or persistent AF is associated with improvements in functional capacity (assessed by peak VO_2_ that is derived from cardiopulmonary exercise test [CPET], activity, and quality of life (QoL) assessed via the Atrial Fibrillation Effect on Quality‐of‐Life [AFEQT] Questionnaire) compared with conventional management.

### Design

2.2

In this study, subjects with drug‐refractory paroxysmal or persistent AF will be randomized to CA with conventional management based on clinical AF recurrence after the CA procedure (control arm) or to an ICM‐guided early intervention strategy (early intervention arm) (Figure 1). This will be a prospective, single‐tertiary center of a large healthcare system, double‐blind (to SCAF data), randomized clinical trial enrolling 120 patients with drug‐refractory paroxysmal or persistent typical AF who have been referred for a CA with ICM monitoring based on conventional clinical indications.

**FIGURE 1 anec13043-fig-0001:**
[figure not shown]
Study design

### Study population

2.3

The patient population for this trial consists of patients with drug‐refractory paroxysmal or persistent AF referred for CA based on conventional clinical indications.

Patients will be stratified in a 1:1 ratio by the type of AF (i.e., paroxysmal vs. persistent AF). The study protocol was approved by the URMC ethics committee and conducted in compliance with standard institutional operating procedures and the Declaration of Helsinki. All patients enrolled in the study will provide written informed consent.

#### Eligibility

2.3.1

Patients with *paroxysmal AF* refractory or intolerant to at least one antiarrhythmic agent, according to current guideline indications for paroxysmal AF ablation (Class I); (January et al., 2014, 2019) or patients with *persistent AF* refractory or intolerant to at least one antiarrhythmic agent, according to current guideline indications for persistent AF ablation (Class IIa) (January et al., 2014, 2019).50 years of age or olderCHA_2_DS_2_‐VASc ≥2 in men or ≥3 in women at the time of consentUndergoing CA for AF for the first timeICM indicated for monitoring symptoms after AF ablation as standard of careSigned informed consent and willing to comply with the study protocol

#### Exclusions

2.3.2

Inability to tolerate any AAD therapySustained AF lasting more than 3 yearsLeft atrial diameter of 60 mm or greaterInability to undergo AF CA (e.g., presence of a left atrial thrombus, contraindication to anticoagulation)Prior ablation for an atrial arrhythmia, either by catheter or by surgeryNYHA class IV congestive heart failurePatients with an implantable cardiac rhythm device (ICD/CRTD/PPM)LV ejection fraction ≤35% if indicated for an ICDCoronary revascularization or valve surgery within 3 months prior to consent dayPrior valve surgery using a mechanical prosthesisLife expectancy <1 year for any medical conditionUnwillingness to comply with all postprocedural follow‐up requirements and to sign informed consentPatients with metabolic derangements (e.g., renal/hepatic failure, electrolyte disturbance, etc.), prohibiting electrophysiology study and ablation or AAD medical therapy (e.g., dofetilide, sotalol, or amiodarone, etc.)Patients with an intracardiac thrombusPregnancy or nursingContraindication to anticoagulant therapy

### Study design

2.4

The design of the study and the schedule of activities are presented in Figure 1 and Table 1, respectively. This will be a prospective, single‐tertiary center (of a large Healthcare System in Upstate New York), double‐blind (to SCAF data), randomized clinical trial enrolling 120 patients with drug‐refractory paroxysmal or persistent typical AF who have been referred for a CA with ICM monitoring based on conventional clinical indications.

**TABLE 1 anec13043-tbl-0001:** Scheduled activities

Reportable data items	Screening/enrollment/randomization	Follow‐up visits				
	Visit 1	Tele‐visit 2	Tele‐visit 3	Tele‐visit 4	Tele‐visit 5	Clinic visit 6
		1 month after randomization +/− 14 days	3 months after randomization +/− 30 days	6 months after randomization +/− 30 days	12 months after randomization +/− 30 days	15 months after randomization +/− 30 days
Inclusion/Exclusion	√					
Informed consent	√					
Demographics	√					
Medical History	√					
Physical exam	√					√
Cardiac Medications	√	√	√	√	√	√
NYHA class	√	√	√	√	√	√
12‐lead ECG (most recent)^a^	√	√	√	√	√	√
Echo (most recent)^a^	√					
AFEQT^b^	*√*					*√*
CPET	√					√
AF ablation^a^	√					
ICM insertion^a^	*√*					
ICM data collection^c^		*√*	*√*	*√*	√	√
Repeat procedures/change in medications		√	√	√	√	√
Healthcare utilization^d^		√	√	√	√	√
Adverse Events^e^		√	√	√	√	√
Protocol deviations		√	√	√	√	√
Subject status		√	√	√	√	√

^a^
Standard of care procedures.

^b^
QualiTy‐of‐life (AFEQT) questionnaire will be used to assess QoL.

^c^
Interrogation committee will meet on a monthly basis.

^d^
defined as unplanned hospitalizations, ED visits, cardioversions, and unplanned office visits (beyond those designated as study visits).

^e^
defined as unplanned hospitalizations, ED visits, and cardioversions.

#### Recruitment

2.4.1

Recruitment will occur at the University of Rochester Healthcare System, comprising three hospitals and associated outpatient clinics in Upstate New York. Screening for enrollment will be conducted in compliance with HIPPA requirements. Subjects who meet the eligibility criteria and do not have any exclusions will be recruited by the clinical electrophysiology groups associated with URMC.

#### Consent

2.4.2

The study, including the entailed procedure's possible benefits and risk, will be discussed with the patient. A brochure which contains detailed information in regard to the study will be provided to all subjects. The patient will be required to sign a consent for participation in ICM‐REDUCE‐AF.

#### Randomization

2.4.3

Study subjects will be randomized 1:1 to conventional management based on clinical AF recurrence after the CA procedure (control arm) or to an ICM‐guided early intervention strategy (early intervention arm), with prespecified arrhythmic, clinical, functional, and QoL endpoints.

#### Baseline evaluation

2.4.4

After enrollment and randomization, baseline testing will be performed including a clinical history, physical exam, 12–lead ECG, echocardiogram, CPET, and QoL assessed by the AFEQT questionnaire. CPET will be performed in the rhythm (sinus rhythm vs. AF) the patient is presenting with day of their testing.

#### Follow‐up

2.4.5

Following baseline testing, patients will undergo AF ablation with ICM insertion per standard clinical practice and will be followed over 15 months (comprising the 3‐month blanking period and the subsequent 12 months of follow‐up for AF burden assessment). Subsequent study visits will be virtual (through phone contact and/or videoconferencing) in which: (a) remote ICM interrogations will be transmitted to the Data Coordination Center (DCC) by the site research coordinator; (b) follow‐up data on subject status and healthcare utilization/adverse events will be obtained; (c) AF management will be adjusted based on the prespecified study protocol supervised by the DCC. CPET, and QoL testing will be repeated at the 15‐month follow‐up visit.

#### 
Post‐AF ablation management in the early intervention arm

2.4.6

In the early intervention arm, the DCC study manager will transmit electronic notifications to the site principal investigator (PI) and research coordinator on the recommended treatment change (i.e., antiarrhythmic drug resumption and/or repeat ablation) based on adjudicated detection of SCAF and patient‐triggered mobile app AF transmissions. Based on data on the duration of AF that is associated with increased risk of progression, SCAF requiring early intervention will be defined in the present study as ≥2 episodes lasting >5 min but <6 h or one episode lasting >6 h. Physicians and patients will be blinded to ICM interrogations. If SCAF is detected by ICM adjudication or if a patient‐triggered mobile app transmission is confirmed as AF at the DCC, the study manager at the DCC will send electronic notifications to the site PI and research coordinator on the protocol recommendations (Figure 2a).

**FIGURE 2 anec13043-fig-0002:**
[figure not shown]
Study protocol. *Clinical AF episodes in both arms will be confirmed by the ICM. AAD, antiarrhythmic drugs; AF, atrial fibrillation; HR, heart rate; ICM, insertable cardiac monitor; SCAF, subclinical atrial fibrillation

*Management during the blanking period*: Similar to the control arm, medical therapy with AAD in the intervention arm will continue for 3 months after the index CA procedure arm. Symptomatic AF recurrence during the blanking period will be treated with cardioversions. If SCAF is detected by the ICM or symptomatic AF recurrence occurs after one‐month postablation (i.e., during the second or third months), AAD therapy will not be discontinued at the 3 months per protocol. AF recurrence during the blanking period will not be an indication for repeat ablation.

*Management after the blanking period*: If SCAF recurrence is detected by ICM adjudication or if symptoms resulting in a patient‐triggered mobile app transmission are confirmed as AF, the study manager at the DCC will send electronic notifications to the site PI and research coordinator on the protocol recommendation for AAD therapy resumption (if discontinued at 3 months) or for referral for reablation (if already on AAD therapy). Clinical AF recurrence in the early intervention arm will be managed using the same protocol as in the control arm (Figure 2a).

#### 
Post‐AF ablation management in the control arm

2.4.7

Management in the control arm will be protocoled based on clinical AF recurrences (Figure 2b). Physicians and patients will be blinded to SCAF detected by the ICM but will be provided by the DCC upon request with full ICM information on any clinical episodes.

*Management during the blanking period (≤3 months)*: Medical therapy with AAD will continue for 3 months in all study patients after the index CA procedure. Clinical recurrences during the blanking period will be treated with cardioversions and/or AAD intensification. Discontinuation of AAD therapy after the blanking period is recommended for all patients in the control arm.

*Management after the blanking period (>3 months)*: Upon the development of clinical AF recurrence after the blanking period (defined as symptoms resulting in medical contact, confirmed by the ICM as AF episodes > 5 min), treatment with AAD will be resumed. If a second clinical AF recurs despite AAD, repeat ablation is to be performed. The DCC will provide ICM data on clinical episodes upon request by the treating physician, as well as complete data on all ventricular arrhythmic events. Data on patient‐triggered mobile app transmissions will also be provided by the DCC upon request to physicians of patients in the control arm but will only be used to guide management in the early intervention arm. ICMs will be opened to physicians upon study closure to provide long‐term arrhythmia monitoring.

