#### Management common to both arms

2.4.8

Physicians and patients in both arms will be blinded to ICM data on SCAF adjudicated by an independent committee that is comprised of three electrophysiologists at the DCC. ICM data on clinical episodes (defined as symptoms resulting in medical contact) will not be blinded and will be made available by the DCC to physicians in both arms upon request. Protocol recommendations will be mandated in both arms unless deemed contraindicated by the treating physician due to a change in the patient's health status after enrollment. ICM interrogations will be done via an electronic system. The blinded data from the ICM interrogations will be sent to the DCC. From this location, if AF requiring intervention is detected in the intervention arm, the adjudicated data are unblinded, and appropriate treatment recommendations are sent to the site PI and research coordinator. The DCC will provide full data on all other ICM‐adjudicated arrhythmic episodes, including ventricular arrhythmias (regardless of symptoms). ICM data will be opened upon study closure (15 months) to provide physicians access for long‐term arrhythmia monitoring.

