### Endpoints

2.5

The primary endpoint of the trial is AF burden between 3 and 15 months after the index CA procedure, as detected by an ICM, which will be inserted prior to or at the time of AF ablation procedure in all study patients. AF recurrence is defined as any episode of AF lasting >30 s per published consensus statements (Calkins et al., 2017). AF burden will be defined as the mean amount of time spent in AF over the prespecified period of time (excluding short AF episodes of ≤30 s).

#### 
Secondary endpoints are

Healthcare utilization, defined as the cumulative total of hospitalizations, ED visits, cardioversions, and office visits (beyond those designated as study visits Table 1) in each arm from the index CA procedure through 15 months.Functional capacity, as assessed by the gold standard of peak VO_2_, which will be determined from CPET performed at baseline and at 15 months.Functional capacity, as assessed by the average daily count of steps derived from the ICM, between baseline and 15 months.QoL measures using the AFEQT questionnaire obtained at baseline and at 15 months.

#### 
Tertiary (exploratory) endpoints are

Clinically significant (>30 min) atrial arrhythmia (AF, atrial flutter, or atrial tachycardia) as detected and documented by ICM after the performance of the index AF ablation procedure (excluding the initial 3‐month blanking period).Symptomatic AF recurrence (regardless of duration), summarized as number of episodes per patient confirmed as AF by the ICM.Adverse events (more severe components of the healthcare utilization endpoint, comprising unplanned hospitalizations, ED visits, and cardioversions).

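### A symptomatic recurrence in months 2–3 leads to opposite AAD rules in the two arms, so a difference in AF burden cannot be credited to acting on ICM data alone

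*Protocol article*

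**What the plan says.** **Intervention arm, blanking period (section 2.4.6).** AAD runs for three months after the index ablation. There are two alternative triggers for not stopping it then: SCAF on the ICM, or a symptomatic recurrence after the first month. The rule reads "i.e., during the second or third months), AAD therapy will not be discontinued at the 3 months per protocol". On acute handling: "Symptomatic AF recurrence during the blanking period will be treated with cardioversions".

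**Control arm, blanking period (section 2.4.7).** The section describes control management as driven by clinical recurrences. AAD again runs for three months, and then "Discontinuation of AAD therapy after the blanking period is recommended for all patients in the control arm". No exception is made for a patient who had a clinical recurrence in month 2 or 3. On acute handling: "Clinical recurrences during the blanking period will be treated with cardioversions and/or AAD intensification".

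**Force and blinding (section 2.4.8).** "Protocol recommendations will be mandated in both arms unless deemed contraindicated by the treating physician", where the exemption is tied to a change in health status after enrolment. Clinical episodes, meaning symptoms that lead to medical contact, are not blinded in either arm.

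**Endpoint and objective.** Section 2.5: "The primary endpoint of the trial is AF burden between 3 and 15 months after the index CA procedure". Section 2.1 asks whether an ICM-guided "early intervention strategy following CA of drug‐refractory paroxysmal or persistent AF will lead to a greater reduction in AF burden".

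**The concern.** Two things are meant to separate the arms: acting on SCAF, and acting on patient-triggered app transmissions, which section 2.4.7 reserves for guiding intervention-arm care. A symptomatic episode that brings the patient to a clinician belongs to neither. It is known to the treating physician in both arms, yet it keeps AAD going in one arm and leaves the stopping recommendation in force in the other.

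The rules part at month 3, which is when the primary window opens, and they part in patients who have just shown recurrent AF. Some of any observed difference in burden could therefore come from an AAD policy that could be applied without looking at SCAF data. What is at stake is the explanation of a positive result: how much is due to acting on ICM information, and how much to continuing a drug after a symptomatic episode.

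**Working it through.** **1. The same event under each arm's rules.** Take a patient with symptomatic AF in month 2 or 3 who contacts a clinician.

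| | Intervention (2.4.6) | Control (2.4.7) |
|---|---|---|
| Known without SCAF data? | Yes | Yes |
| AAD at month 3 | Not stopped | Stopping recommended, no exception |
| Force (2.4.8) | Mandated | Mandated |
| Acute handling in blanking | Cardioversion | Cardioversion and/or AAD intensification |

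The terms differ (symptomatic in one section, clinical in the other), but a symptomatic recurrence with medical contact falls under both.

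**2. Who is affected beyond the intended contrast.** A symptomatic patient whose ICM also meets the SCAF definition (at least two episodes over 5 min but under 6 h, or one over 6 h) would stay on AAD through ICM guidance anyway. A patient whose symptoms arrive as a confirmed app transmission is also within the intended intervention. The unintended part is limited to symptomatic patients with medical contact who meet neither trigger. The document does not say how many there are.

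**3. The plan's own power figure, for scale.** Inputs from section 2.6: control burden 5.3% (SD 2.6%) in paroxysmal and 25% (SD 12%) in persistent AF, 60 per arm, one-sided 0.05. I read the 1:1 stratification in section 2.3 as 30 + 30 per arm and take equal SDs in the two arms.

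- Mean = (5.3 + 25)/2 = 15.15%.
- Within-stratum SD = √[(2.6² + 12²)/2] = 8.68%.
- Standard error of the difference = 8.68 × √(2/60) = 1.585.
- Power = Φ(r × 15.15/1.585 − 1.645), giving 88.9%, 98.5% and 99.9% for r = 30%, 40% and 50%.

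This matches the stated 89%–99.9%. No stated figure is wrong on this point.

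**4. Illustration of size; all three inputs are assumed.** Let p be the share of patients with a symptomatic recurrence in months 2–3 (10%–30%), k their burden relative to the arm mean (1–2), and a the relative reduction from staying on AAD (30%–50%). With no effect of ICM information, the relative reduction in the arm mean is p × k × a.

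| p | k | a | Reduction | Share of planned 40% | Chance the test rejects |
|---|---|---|---|---|---|
| 10% | 1 | 30% | 3% | 7.5% | 8.7% |
| 20% | 2 | 30% | 12% | 30% | 31% |
| 30% | 2 | 50% | 30% | 75% | 89% |

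**5. Why the upper end is unlikely.** The formula counts every symptomatic patient and holds the AAD contrast for the full 12 months. If half of these patients met the SCAF or app trigger anyway, 12% becomes 0.5 × 12% = 6%. If control patients also resumed AAD halfway through the window, with burden spread evenly, it becomes 0.5 × 6% = 3%. Both halvings are assumptions. They show only the direction and rough strength of the two limits.

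**The case against.** **The trial compares strategies.** Sections 2.1, 2.2 and 2.4.3 set an ICM-guided strategy against conventional management. No objective promises to isolate the SCAF component, and randomisation protects the comparison of the two packages. This stands. A reader might infer that the trial is invalid or that its question goes unanswered; the documents do not support that. Only attribution to acting on ICM data is weakened.

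**The protocol does not break its own promise of equal management.** A reader might infer a direct contradiction from "Clinical AF recurrence in the early intervention arm will be managed using the same protocol as in the control arm". That sentence stands under management after the blanking period and does not govern months 1–3. The tension lies elsewhere: control care is described as driven by clinical recurrences, yet its month-3 rule takes no account of them.

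**Acute treatment.** A reader might count the different cardioversion and AAD-intensification wording as further bias towards the intervention. It does not support that. It applies before the primary window, gives controls more options, and may be no more than condensed wording, since section 2.4.6 does not exclude intensification.

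**Overlap and catch-up.** Some symptomatic patients meet an ICM or app trigger anyway, and section 2.4.7 has controls resume AAD at the first post-blanking clinical recurrence. Both points stand and shrink the effect. Neither removes the different rules.

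**Missing detail.** This is a condensed article, and the algorithms in Figures 2a and 2b could not be read for this check; they may narrow or settle the difference. The text itself is clear on both month-3 rules, and section 2.4.8 answers the argument that a recommendation is optional.

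**Conclusion.** The point holds in a limited form. For symptomatic patients with medical contact in months 2–3 who meet neither the SCAF nor the app trigger, the arms follow different AAD rules that need no ICM guidance, from the moment the primary window opens. The strategies are still validly compared, but a difference in AF burden cannot be credited to acting on ICM data alone.

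The size cannot be derived from the document. The 3%–30% relative reduction rests wholly on assumed values of p, k and a, with the upper end unlikely for the reasons given. It should not be read as an estimate of bias. The rejection probabilities also depend on the within-stratum SD that reproduces the plan's power. No view is taken on which AAD rule is clinically right.

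**What to change.** Reconcile sections 2.4.6 and 2.4.7 and Figure 2 so that a clinical recurrence in the blanking period follows one rule in both arms, with the clinical team choosing the rule. The arms would then differ in the blanking period only by action on SCAF and app-transmitted AF. Using one term, defined as in section 2.4.8, for such a recurrence in both sections would remove the symptomatic/clinical ambiguity.

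If the difference is deliberate, say so, state that the trial tests the whole management package including its AAD policy, and limit the conclusion accordingly.

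The first route costs a text amendment, with no added patients or visits. The second costs a slightly narrower conclusion.
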